### Allocation to treatment groups

To assess the acceptability of the intervention and proposed outcome measures for use in a definitive trial across an ethnically diverse sample, recruited schools will be stratified based on the ethnic composition of their pupils (identified above). Schools within each stratum will be randomised into the two study arms (intervention and control, using an allocation ratio of 1:1) by an independent statistician at the Leicester Clinical Trials Unit (CTU) following the completion of baseline measurements. Two schools with predominantly South Asian pupils and two schools with predominantly White British pupils will be randomised into the intervention and control arms (four schools in each arm). Stratification of schools will enable us to examine whether there are ethnic differences in terms of participant recruitment and retention, adherence to the outcome measures, and preliminary effects of the intervention on outcome measures. The statistician performing the analyses will be blinded to the schools allocation to the study arms, as will the community researchers undertaking the outcome measurements.

### Experimental intervention

Six sit-stand desks will be placed in one year 5 classroom (replacing standard desks) in each intervention school for two school terms. The research team will support teachers in the development of a rotation plan to ensure that all children in their class are exposed to the sit-stand desks for at least 1 h/day on average across the week. Stools or chairs will remain and children will be free to choose whether they sit or stand. Teachers and pupils in the intervention classrooms will receive training on sit-stand desk use by the research team. Teachers will also receive a Professional Development Manual containing information on the health benefits of reducing prolonged sitting and information on correct posture when standing at the desks. The manual and training will focus on encouraging correct adoption of the intervention targeting key barriers and facilitators to sit-stand desk use, identified from our previous work [6, 33] and from the Capability, Opportunity, and Motivation to perform a Behaviour (COM-B) model within the Behaviour Change Wheel [34] and the Theoretical Domains Framework [35] (e.g. self-efficacy, motivation and knowledge). Standardised behaviour change techniques (e.g. goal setting, instruction) [36] will also be used. A summary of the intervention components is shown in Table 1 and Fig. 3 represents a simple logic model for the Stand Out in Class intervention. Additional file 1 details potential intervention barriers, solutions and hypothesised mediating processes informed by the above theoretical frameworks.

**Table 1 Tab1:** Components of the Stand Out in Class intervention

Intervention component	Target domain	Meditating variable	Description
Adjustable sit-stand desks	Environment	Exposure to desks	Six adjustable sit-stand desks introduced into the classroom
Nudging prompts	Environment	Children choose to stand rather than sit when using desks	Stickers placed upon each of the sit-stand desks • Have you stood up this lesson? • Standing tall and proud this lesson?
2-h one-to-one meeting	Teacher	Exposure to desks	2-h meeting with teacher which will cover: - Why it is important to increase standing/reduce sitting - Importance of exposure to sit-stand desks - Safety—how to use the desks - Rotation plan and example, plus creation of a rotation plan for the following 2 weeks
Professional Development Manual	Teacher	Exposure to desks	Cover topics such as - Why it is important to increase standing/reduce sitting - Importance of exposure to sit-stand desks - Safety—how to use the desks - Rotation plan example
Planned weekly rotation plan	Teacher	Exposure to desks	Teacher creates a predetermined rotation plan and keeps a record of whether this was met or not—simple tick sheet
Fortnightly support with practitioners	Teacher	Exposure to desks	Phone or face-to-face meeting with researchers/practitioners—discuss any issues around implementation of rotation plans.
30-min workshop	Children	Exposure to desks Children choose to stand rather than sit when using desks	Cover topics such as - Why it is important to increase standing/reduce sitting - Importance of exposure to sit-stand desks - Safety—how to use the desks - Rotation plan and how it will work - Discuss other intervention aspects—social contract and competition
Standing champion/leader	Children	Exposure to desks Children choose to stand rather than sit when using desks	One child in a group is chosen as a standing champion with responsibility of reminding the teacher of the rotation plan.
Group contract	Children	Exposure to desks Children choose to stand rather than sit when using desks	Children are all asked to sign a large contract which will state: I will try my best to - Stand up in a good posture when using the sit-stand desk. - Not to disturb the class when I stand up at my sit-stand desk. - Remember when it is my turn to use the sit-stand desk. - Be very careful not to hurt myself or other people when I use the sit-stand desk.

**Fig. 3 Fig3:**
[figure not shown]
A simplified logic model linking the Stand Out in Class intervention components to hypothesised mediating processes and the primary outcome

### Control arm

To compare the effects of the intervention against usual practice (i.e. the provision of standard classroom desks), schools assigned to the control arm will be requested to continue with their usual practice and lesson delivery, no environmental changes will be made to their classrooms. The year 5 participants in the control schools will be asked to complete the same study measurements as those in the intervention schools at the same time points. Upon completion of the study, control schools will receive a report summarising their pupils’ sitting and physical activity data. They will also receive adapted materials (i.e. the Professional Development Manual provided to teachers in the intervention schools outlining the benefits of reducing sitting but excluding references to sit-stand desks) upon completion of all follow-up evaluation measures.

### Measurements

#### Trial feasibility-related outcomes

The predominant aim of this pilot study is to establish school and participant recruitment and retention rates, acceptability of the intervention and proposed outcome measures, intervention and measurement fidelity, and the availability and completeness of economic data for an estimation of potential cost-effectiveness in order to inform the development of a fully powered definitive trial. Study uptake will be monitored by recording the number of schools and pupils approached, and the number agreeing to participate (objective 1). Withdrawal rates of schools and children (objective 2) and completion rates for outcome measures will be summarised (objective 3), and these feasibility outcomes will be compared between ethnic groups (objective 4).

#### Process evaluation

A series of interviews and focus groups with teachers, children and parents will be conducted following the completion of baseline measures and randomisation to explore the acceptability of trial procedures, including randomisation (objective 5), and the acceptability of the measurement instruments (objective 6). Eight one-to-one interviews (one per teacher) will be undertaken with the participating year 5 teachers during this phase of the process evaluation, and eight separate focus groups (one per school) will be undertaken with children and parents. We will aim to recruit between four and six participants for each focus group conducted throughout the process evaluation. Acceptability of the intervention (objective 7), and children’s, teacher’s and parent’s perceptions and experiences of the intervention and outcome measures (including any negative effects such as discomfort from the monitoring equipment, reasons for non-compliance to the outcome measures, or class disruption) will be obtained during the intervention through a further set of interviews (*n* = 4, with teachers from the intervention schools) and focus groups (four with children and four with parents from the intervention schools) (objective 8). Differences in trial and intervention acceptability between ethnic groups will be explored as part of the analyses from the focus groups (objective 4). Towards the end of the intervention, four one-to-one interviews will be conducted (one per intervention school) with senior staff (head teachers/deputy head teachers) to further examine the acceptability of the intervention (objective 7). Table 2 provides a detailed plan of the measures and methodologies which will be used in the process evaluation.

**Table 2 Tab2:** The Stand Out in Class pilot RCT process evaluation plan

Areas to measure	General process questions	Data source and data collection method	Total numbers and sampling strategy
Acceptability of randomisation and measurement tools (objectives 5 and 6)	How did schools feel about being randomised to intervention/control arms? How did schools/children/parents experience recruitment and outcome assessments? Did schools/children/parents find outcome assessments acceptable? What were the reasons for not participating in the trial and/or not complying to the outcome measures?	Interviews with teachers In-class focus groups with children Focus groups with parents Recruitment data (numbers consenting), and missing data from outcome assessments One-to-one interviews with parents and children not participating and/or not complying	Eight teachers from participating schools (end of summer term) Eight focus groups with children (one per school) after baseline assessments. Eight focus groups with parents (one per school) after baseline assessments. Data collected at baseline and follow-up Interviews conducted after baseline assessments
Intervention acceptability and fidelity (objectives 7 and 9)	Was the intervention implemented as planned?	Interviews with intervention teachers Observations of lessons	Four intervention teachers Time-points (T): T1: After desk installation T2: End of year 5 Four intervention schools observed once per term
Intervention acceptability and fidelity (objectives 7 and 9)	What proportion of the target group participated in the intervention?	Teachers logs and telephone interviews with intervention teachers	Four intervention teachers recording use of desks in log book and brief telephone contact every 2 weeks
Intervention acceptability and fidelity—potential moderating factors (objectives 7 and 9)	How were children engaged with sit-stand desks? How satisfied were schools/children/parents with sit-stand desks? How did schools/children/parents perceive the outcomes and usefulness of sit-stand desks	Focus groups with children (in class) Interviews with teachers Focus groups with parents	Four in class focus groups with children from intervention schools: Time points: T1: After desk installation T2: End of year 5 Four intervention teachers T1: After desk installation T2: End of year 5 Four parent focus groups from intervention schools (after desk installation)
Intervention acceptability and fidelity—strategies to facilitate implementation (objective 7 and 9)	What strategies were used to support introduction of standing desks? How were these strategies perceived by staff involved within project?	Interviews with teachers	Four intervention teachers Time-points: T1: After desk installation T2: End of year 5
Intervention acceptability and fidelity—quality of delivery (objectives 7 and 9)	How well were sit-stand desks introduced? What is the quality of the sit-stand desks and professional manual?	Interviews with teachers Focus groups with children (in class)	Four intervention teachers Time-points: T1: After desk installation T2: End of year 5 4 in class focus groups with children from intervention schools: T1: After desk installation T2: End of year 5
Intervention fidelity—context (objective 9)	What factors at political, economical, organisational and work group levels affected the implementation?	Interviews with teachers and head teachers	Four intervention teachers (end of year 5) Four interviews with head teachers from intervention schools (end of year 5)

To assess intervention, fidelity intervention classrooms will be observed by a member of the research team for a duration of at least half a school day during the Spring and Summer terms. These classroom observations will take place once per school term (Spring and Summer) for each intervention school (eight observations in total, two per intervention school). During these observations, every 10 min the researcher will record the number of boys and girls who are sitting or standing when using the sit-stand desks. Field notes will also be taken to document the occurrence of any intervention components (i.e. use of prompt cards, engagement with a standing champion, see Table 1) during the observation period. Children’s posture during sit-stand desk use will also be recorded using a postural analysis recording system based on the Portable Ergonomic Observation (PEO) [21] to assess any future risk of musculoskeletal injury (objectives 8 and 9).

#### Health- and education-related outcome measures

All health-related outcome measurements will be taken twice, at baseline prior to randomisation, and approximately 6 months after baseline when pupils are at the end of year 5. The likely primary outcome in a definitive trial would be change in average daily school-day sitting time. Sitting will be measured objectively for seven consecutive days during each measurement period using the activPAL3 micro accelerometer. The activPAL3 will be waterproofed (using a nitrile sleeve and hypoallergenic Hypafix [BSN Medical] dressing) and participants will be requested to wear the device continuously (24 h/day) on the anterior aspect of their right thigh during each measurement period. Participants will be provided with a brief diary during each monitoring period where they will be requested to document time in bed and any periods of non-wear.

The use of the activPAL to objectively measure sitting has increased in recent years [37], and the device has been successfully used as a primary outcome measure in previous school-based sedentary behaviour interventions [6, 17, 24] and is recommended for use in interventions when the primary outcome measure is sitting [38]. It is regarded as the most accurate method of assessing sitting behaviour in free-living settings [39] and has been shown to be almost 100% accurate in measuring sitting, standing, walking and postural transitions in children [40, 41]. Whilst total daily school-day sitting time is likely to be the primary outcome for a future trial, we will also extract classroom and leisure-time sitting, standing and stepping time, along with the number of transitions between sitting and standing from the activPAL data. Periods of non-wear and sleep time will be excluded from the analyses using an automated algorithm [42], supplemented with cross-checking against participant’s diary entries. We will examine any positive (i.e. reductions in sitting) or compensatory effects (increases in sitting) of the intervention on children’s behaviour out of school hours. The variability (standard deviation) of the data from the proposed primary outcome will be used to inform a sample size calculation for a definitive trial (objective 11).

Proposed secondary outcomes for a definitive trial include objectively measured physical activity. While the activPAL provides a valid measure of posture, it has not been well validated for assessment of various physical activity intensities among children. Therefore, children will wear the ActiGraph GT3X+ accelerometer on the waist continuously (24 h/day) for seven consecutive days, concurrently with the activPAL, during each measurement period. Periods of non-wear will be documented in a brief diary provided with the devices. Waist worn accelerometers have traditionally been considered the criterion measure of children’s physical activity [43]. The ActiGraph is the most commonly used accelerometer in field-based research and has been shown to have acceptable reliability and validity in paediatric populations [44]. Times spent in light (26–573 counts per 15 s epoch) and moderate-to-vigorous intensity (≥ 574 counts per 15 s epoch) activity throughout the day, and during and out of school hours will be extracted from the ActiGraph data using the Evenson cut-points [45]. In a comparative study examining the classification accuracy of five different ActiGraph cut-points for determining children’s and adolescent’s physical activity intensity, against indirect calorimetry, the Evenson cut-points were highlighted as the most accurate across all intensity levels and are therefore recommended for use in this age group [46]. Periods of non-wear and sleep time will be excluded from the analyses during the processing of the ActiGraph data, supplemented with cross-checking against participant’s diary entries.

At each measurement point, children’s stature and body mass (both assessed without shoes) will be measured directly using standard procedures by trained research staff and BMI will be calculated and converted to a BMI percentile based on UK reference data [47]. Body composition (percentage body fat and fat mass) will be assessed via bio-impedance analysis, using Tanita DC-360S body composition scales which contain specific algorithms for children. Blood pressure will be measured from the left arm after at least a 5-min period of quiet sitting using a semi-automated recorder (Omron HEM-907) with a paediatric cuff, in accordance with current recommendations [48]. Three measurements of blood pressure will be taken; each measurement will be separated by a 2-min rest period. The mean systolic and diastolic blood pressures recorded from the second and third assessments will be calculated and used in the analyses.

A set of objective cognitive function tests will also be administered via a validated software package. The software will be installed on school computers enabling a group of students (those with parental consent to participate in the intervention evaluation) to undertake these assessments at the same time in the classroom under the supervision of two researchers. Participants will undertake a practise run through of the cognitive function test battery a day before the test day. The cognitive function test battery will take children approximately 15 min to complete and will include the Corsi block tapping test [49], the Stroop test [50] and the rapid visual information processing (RVIP) task [51]. The Corsi block tapping test is a measure of visuo-spatial working memory capacity [49]. Performance on the Corsi block tapping test is linearly associated with age in typically developing children [52], and the original version has exhibited a test-retest reliability coefficient of 0.7 (Pearson’s correlation coefficient) in 11-year-olds [53]. The Stroop test measures sensitivity to interference and the ability to suppress an automated response (reading colour names in favour of naming the font colour); it is a commonly used measure of selective attention and executive function [54]. The complex reaction time measure within the computerised Stroop test has been shown to exhibit a test-retest reliability of 0.55 (Pearson’s correlation coefficient) in a combined sample of children and adults [55]. The RVIP is a measure of sustained attention and has been shown to exhibit an internal reliability coefficient (assessed using Cronbach’s alpha) of 0.49 in school-age children [56].

Measures of pupils’ academic progress and attainment will be collected using routine assessment data collected by the schools at half-termly intervals. The impact of the intervention on pupil’s behaviour will be assessed using the Strengths and Difficulties questionnaire completed by teachers at baseline and follow-up. This questionnaire, when completed by teachers, has been shown to provide a valid indicator of children’s behaviour (convergent validity: Pearson’s correlation coefficient with the Rutter questionnaire = 0.92 [57]). Children will also report their engagement and disaffection with their own learning [58] (correlation coefficients between pupil and teacher reports of the components of engagement using this measure range from 0.26 to 0.44 [59]) and their postural comfort [21]. In addition, the Paediatric Quality of Life Inventory (PEDS-QL) [60] and EuroQol 5-dimension Youth (EQ-5D-Y) [61] will be completed by children to provide a measure of self-reported quality of life at each measurement point. The construct validity of the PEDS-QL has been previously demonstrated with healthy children displaying significantly higher scores on this measure in comparison to acutely or chronically ill children [60]. Responses on the EQ-5D-Y have been shown to correlate with other measures of children’s health-related quality of life (convergent validity correlation coefficients up to 0.56 [62]). To further inform the economic analysis (objective 12), teachers and parents will also complete a questionnaire (created for the purpose of this study) assessing participants’ health- and education-related resource use at baseline and follow-up. Basic demographic information (sex, age, ethnicity and postcode to determine Index of Multiple Deprivation (IMD) as an indicator of socio-economic status) will be collected at baseline.

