### Study aim and objectives

The aim of this study is to undertake a pilot cluster RCT of the introduction of sit-stand desks in primary school classrooms to inform a future fully-powered definitive trial. A definitive trial would examine the impact of the introduction of sit-stand desks over one school year on weekday sitting time (the primary outcome), health and education related outcomes, with sub-group analyses for ethnicity. To inform such a trial, key information needs to be established around school and participant recruitment, acceptability of the intervention and outcome measures, and attrition rates. The objectives of this pilot study are therefore to

1. Establish and refine a recruitment strategy for schools and pupils.

2. Determine attrition in the trial (schools and children).

3. Determine completion rates for outcome measures (and whether these are sufficiently high to provide accurate data in a full trial).

4. Assess whether there are any differences in trial recruitment, retention and acceptability between ethnic groups.

5. Assess the acceptability of randomisation to schools to the intervention or standard practice.

6. Assess the acceptability of measurement instruments to teachers, children and parents, including the activPAL inclinometer as the tool for the measurement of the primary outcome.

7. Assess the acceptability of the intervention to teachers, children and parents.

8. Monitor any adverse effects, such as musculoskeletal discomfort and/or disruption to the classroom environment/teaching and learning to inform the design of a full trial and minimise or eliminate any such effects.

9. Assess intervention fidelity.

10. Derive preliminary estimates of the effect of the intervention on children’s total daily sitting time, physical activity, indicators of health (markers of adiposity and blood pressure), cognitive function, quality of life, and academic performance, engagement and behaviour.

11. Estimate the standard deviation of the primary outcome to inform a sample size calculation for a full RCT.

12. Determine availability and completeness of economic data and conduct a preliminary assessment of potential cost-effectiveness.

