### Setting

This study will be conducted in primary schools in Bradford. Bradford was chosen as the study location given its ethnic composition (predominantly South Asian and White British) and high levels of deprivation, health inequalities and childhood morbidity [28]. In 2016–17, 38% of year 6 children in Bradford were overweight or obese according to the National Child Measurement Programme [29]. Half of all babies born in Bradford are of South Asian origin and 60% are born into the poorest 20% of the population [28], with elevated risk factors for chronic diseases seen in South Asian children in comparison to White children [10, 30]. The setting of this study therefore is fundamental in addressing the important issue of health inequalities, in that the intervention will be accessible to all children. In addition, the location enables us to pilot this intervention under challenging circumstances meaning that if it proves acceptable it is likely to be transferable to most schools.

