### Data analysis

#### Statistical analysis

This study will be analysed and reported according to the Consolidation Standards of Reporting Trials (CONSORT) statement for cluster RCTs [64]. Data will be analysed on a complete-case basis. The purpose of the primary analysis is to assess the feasibility of recruitment and adherence/retention of primary schools and pupils to a sit-stand desk intervention. As this is a pilot trial, the primary analyses will mainly utilise descriptive statistics. We will summarise the number of schools approached, the number agreeing to participate, the proportion of children within each school with parental consent to participate in the study evaluation, the number of children completing the study protocol, retention rates, and the number providing valid outcome measurement data at baseline and follow-up. The study acceptability data will be presented for the sample as a whole and stratified according to study arm (intervention and control) and ethnicity (South Asian and White British).

While the main aim of this study is to establish acceptability, feasibility, recruitment rates and sample size to inform a definitive trial, and although effectiveness will unlikely be established with the small sample size, we will examine the primary and secondary outcomes to mimic practice for a full trial. Results from this analysis will be treated as preliminary and interpreted with caution [65, 66]. As the number of clusters is low, cluster summary statistics will be used rather than multi-level modelling [67, 68]. The analysis will be carried out using children as the unit of analysis with change in average total school-day sitting time as the primary outcome. A weighted linear regression model will be used to compare the intervention arms weighted by the number of participants followed up in each cluster and adjusted for baseline total daily sitting time on school days for each cluster. To examine preliminary effects of the intervention on the secondary outcomes, the same analytical approach will be adopted as for the primary outcome (objective 10). These analyses will provide preliminary evidence of the effectiveness of the intervention and will in-part inform the decision of whether a definitive trial should be undertaken.

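### BMI is fixed as a percentile and, by implication, analysed as mean change in percentile, which under-weights heavier and very light children; a z-score from the same reference avoids this at no cost

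*Protocol article*

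**What the plan says.** Under Health- and education-related outcome measures, the protocol article takes height and weight at baseline and about six months later, and states that "BMI will be calculated and converted to a BMI percentile based on UK reference data". No z-score is mentioned. The same paragraph adds two further adiposity measures: "Body composition (percentage body fat and fat mass) will be assessed via bio-impedance analysis".

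Under Statistical analysis, the primary comparison is a linear regression on cluster summaries, weighted by the number followed up and adjusted for the cluster's baseline value, "with change in average total school-day sitting time as the primary outcome". For secondary outcomes, "the same analytical approach will be adopted as for the primary outcome". Objective 10 lists markers of adiposity among the outcomes for which a preliminary effect will be estimated.

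The Setting section reports that in 2016–17 "38% of year 6 children in Bradford were overweight or obese".

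**The concern.** The article names the scale for BMI in one section and the model for secondary outcomes in another, and the two fit poorly together. A percentile is bounded at 0 and 100 and is a non-linear function of the reference z-score. A given shift in z moves a child near the median by several points and a child near either end by very little. A mean of such changes weights children by where they started, and nothing in the protocol says that this weighting is wanted.

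At stake is what the preliminary BMI estimate describes. If the intervention altered BMI mainly in heavier children, the mean percentile change would show less of it than an equal average change in mid-range children. With 38% of local year 6 children overweight or obese, a sizeable part of the sample may lie where the scale is compressed.

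**Working it through.** **Inputs from the protocol article.** BMI as a percentile on UK reference data; change as the form of the primary outcome; the same approach for secondary outcomes; 38% overweight or obese (year 6, Bradford). No stated design figure depends on the BMI scale. The minimum sample, 8 × 15 = 120, reproduces and is unaffected.

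**Assumptions, not in the documents.** Percentile and z are linked by percentile = 100·Φ(z), with Φ the standard normal distribution function. Shifts of -0.1 to -0.25 z are illustrative.

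**Step 1: the same z shift at different starting points.** For a shift d from z₀, the percentile change is 100·[Φ(z₀ + d) − Φ(z₀)]. With d = -0.1:

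| Start | z₀ | Change (points) | Relative to the median |
|---|---|---|---|
| 50th | 0 | -3.98 | 100% |
| 85th | 1.036 | -2.45 | 62% |
| 95th | 1.645 | -1.12 | 28% |
| 98th | 2.054 | -0.54 | 14% |

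The ratio of the 50th to the 98th is 3.98/0.54, about 7. The function is symmetric, so a child at the 2nd percentile who gains 0.1 z moves only +0.54 points. On the z scale every one of these changes has size 0.1.

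**Step 2: does the pattern depend on the chosen shift?** Little. For d = -0.20 the changes are -7.93, -5.15 and -2.42 points at the 50th, 85th and 95th. Across d = -0.10 to -0.25, the change relative to the median is 62–67% at the 85th and 28–32% at the 95th.

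**Step 3: a mixed sample.** Further assumptions: 38% of the children lie above the 85th percentile, and z is normal with SD 1.0 to 1.3. The documents give neither the cut-off nor the SD, and the 38% is for year 6, whereas participants are in year 5. If every child shifts by -0.20 z (simulated):

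- below the 85th percentile, the mean change is -6.1 to -6.7 points;
- above the 85th, it is -2.1 to -2.6 points, or 35–38% of the figure below (2.14/6.12 to 2.56/6.67);
- above the 95th, it is -0.95 to -1.2 points.

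The overall mean is -4.6 to -5.1 points. The 38% of heavier children contribute 0.82 of 4.60 to 0.97 of 5.11 points, that is 18–19%.

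If only the children above the 85th percentile shifted by -0.20, the mean z change would be 0.38 × (-0.20) = -0.076, and the mean percentile change -0.8 to -1.0 points.

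**The case against.** The strongest reply is that the article never says in so many words that change in BMI percentile goes into the regression. It says only that BMI is converted, whereas for blood pressure it states which means enter the analysis. The variable that finally enters a model is often settled in an analysis plan, and one may exist. It is also a secondary outcome of a pilot whose effect estimates the article itself calls preliminary.

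Part of this stands. The analysis of change in percentile is an inference from two sections and should be described as implied. But the percentile is the only reference-adjusted BMI scale named, and the model rule covers all secondary outcomes, so it is the natural reading. The limited role of BMI bears on severity, not on whether z is the better scale.

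A reader might infer more than the document supports:

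- *That the adiposity results as a whole are compromised.* Body-fat percentage and fat mass are also measured and are not percentiles.
- *That the analysis is nearly blind to overweight children.* This fits only the extreme upper tail. At the 85th percentile about 62% of the mid-range signal remains.
- *That planning of the definitive trial would be misled through the standard deviation.* The standard deviation to be carried forward is that of sitting time (objective 11).
- *That Bradford was chosen for its excess weight.* The stated reasons are ethnic mix, deprivation, health inequalities and childhood morbidity; the 38% is given as description.
- *That the scale favours one arm.* The compression applies to both arms. It changes which children count most and does not by itself create a difference where the intervention has no effect.

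**Conclusion.** The point holds in a limited form. The protocol fixes a bounded, non-linear scale for BMI and implies a linear comparison of its mean change. Under the normal link, an equal z shift counts about 62% as much at the 85th percentile as at the median, 28% at the 95th and 14% at the 98th, with the same compression at the lower end. If 38% of the sample lay above the 85th percentile, those children would supply 18–19% of the mean percentile change under a uniform shift of -0.20 z. That last figure rests on an assumed cut-off and spread.

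The consequence is a preliminary BMI estimate that under-represents change in heavier and very light children. The article says that the outcome analyses will partly inform whether to proceed to a definitive trial, but no sample size and no stated progression figure rests on BMI. Severity is low.

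**What to change.** In the outcome section, state that BMI will be converted to a z-score on the same UK reference data, and that this z-score, adjusted for its baseline cluster value, is the BMI variable analysed under the secondary-outcome rule. Keep percentiles for describing weight status at each time point.

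The z-score is best computed directly from the reference rather than recovered from rounded percentiles, since rounding loses most in the tails.

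The cost is a change of wording. Height, weight, age and sex are already collected, percentile and z are one-to-one, and neither the sample of 120 nor the model changes.
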